#### Continuous physical activity monitoring

Participants will wear a Fitbit continuously throughout the study, including during both wake and sleep hours. Fitbit-derived data will be categorized into three activity domains:Protocol-Guided Exercise (PGE): Exercise occurring during supervised, in-lab sessions.Non-Protocol Physical Activity (NPA): Incidental movement and unsupervised activity outside scheduled sessions.Total Physical Activity: Combined PGE + NPA, derived from 24-h Fitbit data.

The primary Fitbit metric will be daily step count, a validated proxy for global movement shown to correlate with cognitive, brain, and cardiometabolic health outcomes in older adults [37]. A secondary metric, calories burned, will offer insight into the metabolic intensity of movement. Step count and caloric expenditure will be examined in relation to cognitive function as well as brain and cardiometabolic biomarker outcomes. Analytical models will include PGE and NPA as independent predictors, which will be modeled separately and jointly to assess differential and additive contributions to primary (cognitive, brain, and cardiometabolic markers), secondary (sleep metrics and exercise measures), and tertiary (light exposure and psychosocial measures) outcomes.

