### Interventional group 1 (exercise only)

Participants randomized to the exercise-only group will engage in an 8-week, home- and site-based exercise intervention designed for older adults across a range of cognitive and physical function levels. All site-based sessions will occur in-person at the study facility under supervision of trained staff. Each week, participants will attend two 60-minute structured exercise sessions, consisting of aerobic training and resistance training. On the remaining five days when subjects will not engage in structured exercise, subjects will be asked to engage in 30 minutes of moderate-intensity walking activities. In-lab exercise protocols will be fully standardized to ensure consistency of exercise dosage and fidelity across participants. The target exercise load will be 270 minutes of moderate-intensity exercise weekly for 8 weeks. Although considered short-term exercise, this exercise dosage has been shown to improve cerebral blood flow, regional brain volume, and brain-protective trophic factors [32].

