#### Home-based protocol

In addition to the twice-weekly, site-based exercise sessions, participants will be asked to include 30 minutes of walking at moderate intensity on the remaining five days each week when subjects do not complete the biweekly, in-person exercise sessions.

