#### Analysis strategy

This arm enables a unique opportunity to assess both the independent and combined contributions of sleep and exercise to cognitive, brain, and cardiometabolic outcomes. Statistical models will include main effects for sleep (e.g., adherence to Elemind usage), exercise (e.g., PGE, NPA), and interaction terms to evaluate additive or synergistic effects. Dose-response relationships will be explored using adherence metrics and physiological markers (e.g., heart rate during exercise, sleep efficiency). Adherence to both modalities will be assessed as previously described, summarized descriptively, and modeled as predictors in multivariable analyses of primary outcomes.

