#### Analysis plan

This study is designed as a three-arm, parallel-group trial comparing the effects of an 8-week exercise intervention (group 1), sleep intervention (group 2), and combined sleep + exercise intervention (group 3) on cognitive performance and biomarkers for brain and cardiometabolic health in older adults with MCI or no cognitive impairment. A total of 60 participants (20 per group) will be enrolled. All analyses will be conducted using IBM SPSS Statistics (Version 31.0.0.0; IBM Corp., Armonk, NY, USA). The primary analytic goal is to determine which intervention arm may demonstrate the greatest improvements in cognitive function and biomarker profiles. Descriptive statistics (means, standard deviations, medians, interquartile ranges, and proportions) will be used to summarize demographic characteristics, intervention adherence, and baseline measures. Primary outcomes will include change**s** in cognitive domain-specific and global cognition scores from the digital cognitive assessments and changes in biomarkers for brain (NfL) and cardiometabolic health (HbA1c, hs-CRP, C-peptide, insulin, total cholesterol, HDL, LDL, triglycerides). Secondary outcomes will include changes in sleep metrics (e.g., sleep efficiency, SWS, REM sleep, and total sleep durations, onset latency, and restlessness, as measured via Elemind) and physical activity/exercise levels (PGE and NPA via Fitbit). Tertiary outcomes will include the role of light exposure (measured via Lys) as a potential modulator of sleep parameters and psychosocial measures (e.g., PROMIS Depression, Social Isolation).

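### The Fitbit split classes the prescribed home walks, 150 of the 270 prescribed weekly minutes, as non-protocol activity, so PGE and NPA do not separate protocol exercise from background movement

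*Protocol article*

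**What the plan says.** **The prescription.** Under Interventional group 1 (exercise only), the protocol article states: "Each week, participants will attend two 60-minute structured exercise sessions, consisting of aerobic training and resistance training". On the other five days, "subjects will be asked to engage in 30 minutes of moderate-intensity walking activities". The same section sets the dose: "The target exercise load will be 270 minutes of moderate-intensity exercise weekly for 8 weeks". The walks are repeated under the heading Home-based protocol, where "participants will be asked to include 30 minutes of walking at moderate intensity on the remaining five days each week". Protocol structure and considerations, for the combined arm, includes the home walking programme too. The sleep-only arm has no walking prescription and wears the Fitbit passively (Device use and sleep monitoring).

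**The measurement.** Continuous physical activity monitoring sorts Fitbit data into domains. The first is "Protocol-Guided Exercise (PGE): Exercise occurring during supervised, in-lab sessions". The second is "Non-Protocol Physical Activity (NPA): Incidental movement and unsupervised activity outside scheduled sessions". The third, Total Physical Activity, is the sum of the two.

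**The use.** The same section enters PGE and NPA as predictors of primary, secondary and tertiary outcomes, separately and jointly, to estimate their differential and additive contributions. Analysis strategy (combined arm) says: "Statistical models will include main effects for sleep (e.g., adherence to Elemind usage), exercise (e.g., PGE, NPA), and interaction terms". Analysis plan lists among the secondary outcomes changes in "physical activity/exercise levels (PGE and NPA via Fitbit".

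**The concern.** The home walks are part of the assigned intervention, but the measurement section leaves them no place except the class labelled non-protocol. Three consequences follow.

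- **PGE does not measure the prescribed dose.** Of two participants with the same session attendance, one may do every home walk and the other none, and their PGE can be identical.
- **NPA does not measure background activity.** In the two exercise arms it adds assigned walking to incidental movement. In a joint PGE/NPA model, any effect of the walks is credited to the term labelled non-protocol.
- **NPA has different content across arms.** Prescribed exercise is part of it in exercise-only and combined, but not in sleep-only. A rise in NPA from baseline in the exercise arms cannot be told apart from adherence to the walks, so a comparison with sleep-only is not a comparison of spontaneous activity.

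The reader at risk is the one who takes these coefficients as evidence on which component of activity matters, which is the kind of signal this pilot is meant to pass on to a larger trial.

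**Working it through.** **Inputs, all from the protocol article**

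- Supervised sessions: 2 per week × 60 min (Interventional group 1).
- Home walks: 5 per week × 30 min (Interventional group 1; Home-based protocol).
- Stated target: 270 min per week (Interventional group 1).
- Session content: 10 min warm-up, 20 min aerobic, 20 min resistance, 10 min stretching (Interventional group 1).
- PGE is supervised in-lab exercise; NPA is incidental and unsupervised activity; Total = PGE + NPA (Continuous physical activity monitoring).

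**Step 1. Reproduce the target.** 2 × 60 + 5 × 30 = 120 + 150 = 270 min per week. The stated figure is reproduced, and only with the walks included.

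**Step 2. Allocate the prescribed minutes by the stated definitions.** The walks are unsupervised and outside scheduled sessions. Total has only two parts, so no other class is available.

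| Arm | Prescribed min/week in PGE | Prescribed min/week in NPA |
|---|---|---|
| Exercise-only | 120 | 150 |
| Combined | 120 | 150 |
| Sleep-only | 0 | 0 |

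Share of the prescribed dose in PGE: 120/270 = 44.4%. Share in NPA: 150/270 = 55.6%. Over 8 weeks this is 960 against 1,200 of 2,160 minutes.

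**Step 3. Sensitivity to what counts as exercise.** Without warm-up and stretching, the sessions give 2 × 40 = 80 min, so PGE holds 80/230 = 34.8% and NPA 150/230 = 65.2%. With aerobic minutes only, the sessions give 2 × 20 = 40 min, so PGE holds 40/190 = 21.1% and NPA 150/190 = 78.9%. Counting whole sessions is thus the reading most favourable to the current definition.

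**Step 4. Prescribed against performed dose.** The documents give no expected home-walk adherence, so it is treated as an assumption *a*, with full session attendance. The walks' share of performed minutes is 150*a* / (120 + 150*a*):

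| Assumed *a* | Walk minutes | Share of performed dose |
|---|---|---|
| 50% | 75 | 75/195 = 38.5% |
| 80% | 120 | 120/240 = 50.0% |
| 100% | 150 | 150/270 = 55.6% |

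The break-even is 120/150 = 80%. The walks are the larger part of the dose performed only above that adherence. The 56% figure describes the dose prescribed.

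**Step 5. Is the gap closed elsewhere?** Adherence and engagement records attendance at in-person sessions and has the Fitbit track daily steps, heart rate and activity duration. That captures the walks but does not identify them. Total Physical Activity also contains them, again mixed with incidental movement. No section separates them within NPA.

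**The case against.** The strongest reply is that little of weight depends on the split.

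- **The main test does not use it.** Analysis plan rests the main test of efficacy on the group × time interaction for cognitive and biomarker outcomes. PGE and NPA are not in that model. This stands, and it limits the severity.
- **The walking data are not lost.** Total Physical Activity and whole-day step count, the primary Fitbit metric, include the walks. This stands, but neither isolates them, and the analysis sections name PGE and NPA.
- **The boundary is objective.** Supervised against unsupervised can be tied to recorded attendance and time-stamped sessions. This also stands. It supports keeping that contrast, but not calling the unsupervised part non-protocol.

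A reader might also infer more than the documents support:

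- *That the dose-response analysis fails.* Analysis strategy bases dose-response on adherence metrics and physiological markers, and does not name PGE for that purpose.
- *That NPA mostly reflects the intervention.* The documents give no usual activity level, so the walks' share of NPA or of its variance cannot be derived. Whether walks add to or replace other movement is equally unknown.
- *That NPA differs in definition between all arms.* Exercise-only and combined share one walking prescription, so the problem arises only in contrasts with sleep-only.
- *That any arm difference in activity is a fault.* An exercise prescription is meant to produce one. The fault is that NPA's label hides its source.

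**Conclusion.** The point holds as a moderate defect in secondary and exploratory analyses. The measurement definitions conflict with the protocol's own prescription: 150 of 270 prescribed weekly minutes (56%) are labelled non-protocol, and PGE covers at most 120 (44%). These figures follow from stated numbers and definitions, with no outside assumption. PGE and NPA coefficients, and NPA comparisons of sleep-only with either exercise arm, cannot be read as protocol against background activity.

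This is a conflict between two stated definitions and a stated prescription, so it is not explained by an article condensing a fuller protocol. It does not bias the randomized comparison on cognition or biomarkers. How far it would distort any one coefficient cannot be computed from the documents, because that depends on walk adherence and usual activity, and neither is given.

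**What to change.** Reconcile Continuous physical activity monitoring with Interventional group 1, Home-based protocol, and Protocol structure and considerations. This is a change of measurement definition only; the exercise prescription stays as it is.

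1. Split the Fitbit data into (a) supervised sessions, (b) prescribed home walks and (c) all remaining activity, with Total = a + b + c. Identify (b) from time-stamped walking bouts on non-session days in the exercise-only and combined arms, confirmed at the existing weekly check-in. In sleep-only, all activity is (c).
2. Define PGE as (a) + (b) and NPA as (c). Use these in Analysis strategy and Analysis plan.
3. Report (a) alone as a sensitivity analysis, since its boundary is the most objective.

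If bouts cannot be identified reliably, the minimum repair is to rename the two classes supervised and unsupervised, state that the second includes the prescribed walks, and not interpret it as non-protocol activity.

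**Cost.** A wording change, a rule for recognising a walk, and one more item at a check-in that already takes place. Some bouts will be misclassified in either direction. If participants are asked to mark walks on the device, there is a small added burden, and forgotten marks are foreseeable, notably among those with MCI, who make up about half the sample. The change should be made before walks accumulate, because unmarked bouts are harder to tell from spontaneous walking later.

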#### Assessment of aerobic capacity

Aerobic capacity will be measured at baseline and after 8 weeks of exercise using the six-minute walk test (6MWT). The 6MWT accurately estimates maximal oxygen uptake capacity (VO2max) using regression equations, including distance walked, sex, age, and body mass index [36].

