#### Adherence and engagement

In order to assess adherence to the exercise sessions, attendance will be recorded for all in-person sessions, and wearable devices (Fitbit) will track daily physical activity, including steps, heart rate, and durations of physical activity. Weekly check-ins (10–15 minutes) via phone or secure teleconference will be conducted and documented to ensure protocol adherence, troubleshoot technical issues, and maintain engagement. All data will be stored in HIPAA-compliant systems. Fitbit and the Digital Neuro-Signature Platform data will be de-identified and linked using secure participant codes. Statistical models will include age, sex, years of educational attainment, employment status (unemployed/employed), socioeconomic status, baseline sleep metrics, baseline physical activity levels, and cognitive status as covariates. By integrating standardized, in-lab exercises, wearable technology, digital cognitive assessments, and multimodal biomarker data, this arm of the *CASE* study aims to explore the cognitive, brain, and cardiometabolic impacts induced by structured exercise in aging adults who are at higher risk for AD using a real-world, ecologically valid framework.

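### Unscaled Fitbit calories are read as movement intensity and related to cardiometabolic markers with no body-size term, so calorie associations with marker levels are confounded by body mass

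*Protocol article*

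**What the plan says.** Under Continuous physical activity monitoring, steps come first: "The primary Fitbit metric will be daily step count, a validated proxy for global movement". Calories come next: "A secondary metric, calories burned, will offer insight into the metabolic intensity of movement". The planned use is explicit: "Step count and caloric expenditure will be examined in relation to cognitive function as well as brain and cardiometabolic biomarker outcomes". The device is worn day and night, and one of its activity domains is defined as "Total Physical Activity: Combined PGE + NPA, derived from 24-h Fitbit data". The article does not say whether calories means the 24-hour total, which includes resting expenditure, or only those attributed to activity.

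Under Adherence and engagement, the statistical models are to include "age, sex, years of educational attainment, employment status (unemployed/employed), socioeconomic status, baseline sleep metrics, baseline physical activity levels, and cognitive status as covariates". Other sections add further terms: baseline amyloid and tau markers (Biomarker collection strategy), perceived benefit (Limitations) and light exposure (Discussion). None is a measure of body size. Body mass index appears only under Assessment of aerobic capacity, where oxygen uptake is estimated "using regression equations, including distance walked, sex, age, and body mass index".

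The first hypothesis in Objectives links lower physical activity to worse cardiometabolic profiles at baseline. That is a comparison of levels between people. The Analysis plan defines the primary outcomes as changes, and tests efficacy with a mixed model containing group, time and their interaction.

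**The concern.** The energy cost of the same movement rises with body mass, and so does resting expenditure. Two people who do identical activity record different calories if their weights differ. Unscaled calories therefore mix body size with activity and cannot be read as intensity.

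Body mass is also plausibly related to HbA1c, insulin, C-peptide, hs-CRP and lipids. It then acts as a common cause of exposure and outcome, and pushes the calorie association toward more activity, worse markers. The trial is meant to detect signals for a larger study. A calorie association that is flattened or wrong-signed would misinform that study, and emphasising effect sizes and intervals does not remove confounding.

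**Working it through.** The documents give no figure to reproduce and no distribution for weight, activity or calories. Every numerical input below is an assumption, except n = 60 (Power and sample size considerations).

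**1. Which moves calories more, body size or activity?** Assume body mass index with mean 28 and SD 5; resting expenditure of 1.2 × (10 kcal per kg plus terms in height, age and sex); and activity energy of MET-hours × weight, with mean 4 and SD 1.5 MET-hours. Weight is body mass index × height², so height cancels from the ratios.

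- Total calories rise by 1.2 × 10 + 4 = 16 kcal per kg. Going from 1 SD below to 1 SD above the mean (10 units of body mass index) changes them by 16 × 10 × height² = 160 × height².
- The same span of activity (3 MET-hours) at the mean body mass index changes them by 3 × 28 × height² = 84 × height².
- Total calories: 160/84 = 1.9, so body size dominates.
- Activity-only calories: (4 × 10)/84 = 0.48, so activity dominates but body size still contributes.

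**2. Spurious correlation when activity has no effect.** Treat calories as mass × activity per kg, with the two independent. Then corr(calories, mass) ≈ CVm/√(CVm² + CVa²), and multiplying by the mass–marker correlation gives the spurious correlation.

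| CV of mass | CV of activity | corr(calories, mass) | mass–marker r | spurious r |
|---|---|---|---|---|
| 0.15 | 0.20 | 0.15/0.250 = 0.60 | 0.3 | 0.18 |
| 0.22 | 0.10 | 0.22/0.242 = 0.91 | 0.5 | 0.46 |
| 0.15 | 0.60 | 0.15/0.618 = 0.24 | 0.3 | 0.07 |
| 0.22 | 0.40 | 0.22/0.457 = 0.48 | 0.5 | 0.24 |

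The two-sided 5% critical value at n = 60 is √(t²/(t² + 58)) = 0.254, with t = 2.00 on 58 degrees of freedom. With activity CV of 10–20% the range is 0.18 to 0.46 and straddles that value. With 40–60% it is 0.07 to 0.24 and lies below it. The direction is the same throughout; the size depends on an unknown input.

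**3. Simulation with a protective effect built in.** n = 200,000; marker level regressed on calories, adjusted for age and sex; activity effect −0.1 to −0.3 SD; body mass index effect +0.2 to +0.4 SD; correlation of body mass index with activity 0 to −0.3; 27 scenarios.

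| Exposure | Without body mass index | Sign reversed | With body mass index |
|---|---|---|---|
| Total calories | +0.04 to +0.36 SD | 27 of 27 | −0.11 to −0.38 SD |
| Activity-only calories | −0.22 to +0.08 SD | 3 of 27 | −0.09 to −0.32 SD |

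Activity-only calories were attenuated in all 27. The three reversals combined the weakest activity effect with a stronger body mass index effect.

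**4. Does the form of the model rescue it?** A second simulation used total calories at follow-up and three pairs of effect sizes.

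| Model for the week-8 marker | Calorie coefficient (SD) |
|---|---|
| Age and sex only | +0.15 to +0.24 |
| Plus baseline activity measured as steps | +0.17 to +0.32 |
| Plus baseline activity measured as calories | −0.15 to −0.55 |
| Plus the baseline marker | +0.03 to +0.04 |
| Plus body mass index | −0.12 to −0.37 |
| Change in marker on change in calories | −0.08 to −0.25 |

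So the answer depends on choices that the article leaves open. Change-on-change keeps the protective sign. Adjusting only for the baseline marker removes most of the bias but still hides the benefit.

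**The case against.** The strongest reply has four parts.

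- **Outcomes are changes.** The Analysis plan analyses change, and stable body mass largely drops out of within-person change. This stands for change-on-change models. It does not cover the baseline hypothesis in Objectives, which concerns levels. There, baseline activity is the exposure, so it cannot also stand in for body size.
- **Baseline activity is already a covariate.** If it is measured in calories, it acts as a proxy for body size and the sign is protected. If it is measured in steps, the article's leading Fitbit metric, the reversal stays. The article does not say which, so this reply holds only in part.
- **The covariate list is not closed, and calories may mean activity calories.** Terms are indeed added in other sections, but none concerns body size, and a list was stated. With activity-only calories, attenuation is the expected result and reversal the exception. That part stands.
- **Calories are a minor exposure.** This stands. They are a secondary Fitbit metric in an exploratory trial.

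A reader might infer that the plan puts the estimated benefit of exercise at risk. The documents do not support that: the group × time model contains no calorie term, and step counts do not scale with mass in this way. A reader might also take 0.18 to 0.46 as the expected spurious correlation. That range depends on a narrow assumed activity CV and falls to 0.07 to 0.24 when a wider one is assumed.

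**Conclusion.** The point holds with limited scope. As written, the plan relates unscaled calories to cardiometabolic markers, reads them as intensity and states no adjustment for body size. In analyses of marker levels, chiefly the baseline hypothesis if calories are the activity measure, this biases the association toward more activity, worse markers.

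The direction follows if body mass worsens the markers. The size does not follow from the documents. Under the assumed inputs the association is attenuated with activity-only calories and reversed with total 24-hour calories. It would be too strong to say that the sign will reverse, because the article specifies neither the type of calories nor the exact models. The randomised comparison and the step-count analyses are untouched, and change-on-change models are much less affected. It is worth correcting because the correction is cheap and the calorie analyses are otherwise hard to interpret.

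**What to change.** For models that relate calories to biomarkers:

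1. State whether calories are the 24-hour total or activity-only.
2. Express them per kg of body weight or as MET-minutes, or add baseline body mass index as a covariate. Only the covariate was checked by simulation. Per-kg scaling suits activity calories best, because in the assumed equation resting expenditure is not proportional to weight.
3. Say whether baseline physical activity, as a covariate, is measured in steps or calories.
4. Drop the reading of unscaled calories as intensity.

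Body mass index need not be required in step-count models on this ground, since the mechanism is specific to calories.

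The cost is height and weight at the baseline visit for all 60 participants, including the sleep-only arm, plus one model term and a few sentences. Body mass index is already needed for the walk-test equation.

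Suggested wording: In models relating Fitbit calories to biomarkers, activity calories will be expressed per kg of baseline body weight; where total calories are used, baseline body mass index will be included as a covariate.
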